#### Safety outcome measures

The key safety outcome measures are treatment-emergent adverse events and abnormal laboratory analytes as defined in the protocol [1] Sect. 10.4.4.2 and 10.4.4.3, respectively. All safety outcome measures are given in Supplementary Table 2 along with references to the sections where they are defined in the protocol [1].

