#### Safety objectives

The safety objectives are to assess the effects of the GKT137831 compared to placebo on the key safety outcome measures (treatment-emergent adverse events and abnormal laboratory analytes) and the other safety outcome measures defined in “Safety outcome measures” section.

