#### Safety analyses

Safety analyses will be based on the safety analysis set described in “Safety analysis set” section. The safety outcomes presented in Supplementary Table 2 will be summarised by group (intervention and placebo). Categorical variables will be summarised using frequencies and percentages, and the continuous variables will be summarised using appropriate central tendency and dispersion measures, and presented either as mean and standard deviation (SD) or median and 25th–75th percentile. Percentage standardized differences between the two groups will be calculated for all variables. A value ≥ 10% difference will be taken as a meaningful difference between the groups. In addition, where possible, a linear mixed model or a generalised linear mixed model will be used with the safety measure at the end of the trial as the outcome, a categorical variable indicating the group structure (intervention or placebo group) as the exposure, and the safety measure at the beginning of the trial as a covariate, also accounting for centre variability. Where appropriate, an estimate of the group effect, 95% confidence interval and *p* value will be presented. The results will be summarised in Table 5.

**Table 5 Tab5:** Safety analyses results using the safety analysis set

Safety outcome measure	Values		Percentage standardized difference	Estimated difference^a^	95% Confidence Interval^a^	*P* value^a^
	Intervention (GKT137831) group (*n* = xxx)	Placebo group (*n* = xxx)				
Treatment-emergent adverse events, *n* (%)						
Abnormal laboratory analytes, *n* (%)						
Abnormal physical examination and vital signs, *n* (%)						
QT corrected electrocardiogram (ECG), mean (SD)						
Treatment-emergent qualitative ECG, *n* (%)						
Concomitant medications, *n* (%)						
Systolic blood pressure (mmHg), mean (SD)						
Diastolic blood pressure (mmHg), mean (SD)						
Heart rate (beats per minute), mean (SD)						
Weight (Kg), mean (SD)						

*SD* standard deviation

^a^ If feasible to carry out testing; in the intervention group compared to the placebo group

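### The single baseline-adjusted safety model does not fit the treatment-emergent rows of Table 5, gives no finite estimate when one arm has no events, and has no stated fallback

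*SAP article*

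**What the plan says.** The section Safety outcome measures states: "The key safety outcome measures are treatment-emergent adverse events and abnormal laboratory analytes". The section Safety objectives sets a comparative aim: "The safety objectives are to assess the effects of the GKT137831 compared to placebo on the key safety outcome measures".

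The Safety analyses section gives two layers.

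- **Descriptive, unconditional.** "Categorical variables will be summarised using frequencies and percentages", and "Percentage standardized differences between the two groups will be calculated for all variables". A value of 10% or more counts as meaningful.
- **Model-based, conditional.** The model sentence begins "In addition, where possible, a linear mixed model or a generalised linear mixed model will be used with the safety measure at the end of". So an end-of-trial value is the outcome, group is the exposure, and the other terms are given as "and the safety measure at the beginning of the trial as a covariate, also accounting for centre variability". Reporting is conditional too: "Where appropriate, an estimate of the group effect, 95% confidence interval and *p* value will be presented". Footnote a to Table 5 limits the last three columns: "If feasible to carry out testing; in the intervention group compared to the placebo group".

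Table 5 has ten rows. Five are n (%) rows: treatment-emergent adverse events, abnormal laboratory analytes, abnormal physical examination and vital signs, treatment-emergent qualitative ECG, and concomitant medications. Five are continuous: QTc, systolic and diastolic blood pressure, heart rate and weight. All ten share one column headed Estimated difference. Safety tests are two-sided at 5% (Confidence intervals and significance level). No test type is named for safety; likelihood ratio tests are named only for subgroup interactions.

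**The concern.** The model suits a quantity measured in everyone at the start and at the end, such as blood pressure. It does not suit two of the five n (%) rows, because a treatment-emergent finding is one that was not there at the start. It also has no finite solution when all the events fall in one arm, which is the pattern a safety comparison most needs to handle.

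The feasibility wording lets the analyst leave the cell empty but does not say what goes there instead. Whether a one-sided harm gets an estimate, and by which test, would be settled after the data are seen. At stake is an interpretable between-arm estimate with an interval for binary harms, including a key safety outcome.

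**Working it through.** The SAP states no figure for the safety analysis, so there is none to reproduce; its power statement concerns UACR and does not bear on this point.

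**Inputs.** The Sample size section expects up to 284 screened, up to 50% screen failure, and 60 completers per arm. I take 284 × 0.5 = 142 randomised in total, so 142 / 2 = 71 per arm. This is an assumption, because the sentence can also be read as 142 in each group. I use 71 and 60 per arm. Event rates and the number of centres are not given, so event counts are illustrative. No link function is named; I assume a logit.

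**Step 1: the covariate in treatment-emergent rows.** Set to zero for everyone, it adds an empty column to intercept and group. The design matrix then has rank 2 out of 3 columns. The term drops out and the group effect survives, but the model fitted is no longer the one specified.

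**Step 2: events in both arms.** A random-centre logistic model without the baseline term works (60 per arm, 12 centres assumed): 45 v 40 gives a log odds ratio of 0.41 (SE 0.41), and 20 v 10 gives 0.92 (SE 0.44).

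**Step 3: events in one arm only, 6 v 0 at 71 per arm.**

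- Logistic fit, group only: the odds ratio is (6 × 71)/(65 × 0), which is infinite. The software stops at a log odds ratio of 22.2 with SE 15,548. The Wald statistic is 22.2/15,548 = 0.0014, p = 0.999. The Wald interval is 22.2 ± 1.96 × 15,548, about -30,450 to 30,500.
- Likelihood ratio: log-likelihood with group is 6 ln(6/71) + 65 ln(65/71) = -20.56; without group, 6 ln(6/142) + 136 ln(136/142) = -24.86. Twice the difference is 8.58 on 1 df, p = 0.003.
- Fisher, two-sided: 2 × (71·70·69·68·67·66)/(142·141·140·139·138·137) = 0.028.
- Risk difference: 6/71 = 8.5 points. Wilson limits are 3.9% to 17.2% for 6/71 and 0% to 5.1% for 0/71. Newcombe lower limit: 8.5 - √((8.5 - 3.9)² + 5.1²) = 1.6 (unrounded inputs). Upper limit: 8.5 + (17.2 - 8.5) = 17.2.
- Adding a random centre effect (60 per arm, 12 centres assumed) does not help: the log odds ratio runs to 36 with no computable SE, and the likelihood ratio p is 0.004.

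**Range of drug-only patterns.**

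| Per arm | Events | Wald p | LR p | Fisher p | Risk difference, points (Newcombe 95% CI) |
|---|---|---|---|---|---|
| 60 | 3 v 0 | 0.999 | 0.040 | 0.244 | 5.0 (-1.9 to 13.7) |
| 60 | 6 v 0 | 0.999 | 0.003 | 0.027 | 10.0 (2.0 to 20.1) |
| 60 | 10 v 0 | 0.999 | 0.0001 | 0.001 | 16.7 (7.2 to 28.0) |
| 71 | 4 v 0 | 0.999 | 0.017 | 0.120 | 5.6 (-0.5 to 13.6) |
| 71 | 6 v 0 | 0.999 | 0.003 | 0.028 | 8.5 (1.6 to 17.2) |

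At 4 v 0 (71 per arm), the choice of test alone decides which side of 5% the result falls.

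**Step 4: the standardised difference as a safeguard.** For 6 v 0 at 71 per arm it is 0.0845/√(0.0845 × 0.9155/2) = 43%, well above 10%. Even 1 v 0 gives 17% (71 per arm) or 18% (60 per arm). With no true difference its standard error is about √(2/n), so P(|d| ≥ 0.10) = 2[1 - Φ(0.10√(n/2))]. This is 0.55 for n = 71 and 0.58 for n = 60.

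**Step 5: the scale.** For 60 v 53 out of 71, the log odds ratio is ln[(60 × 18)/(53 × 11)] = ln 1.85 = 0.62. The percentages differ by 7/71 = 9.9 points. Under a logit link, 0.62 would stand under Estimated difference beside those percentages.

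**The case against.** The strongest reply is that the model is only an addition, fitted and reported where it can be. The plan never says that it needs events in both arms. Counts, percentages and standardised differences are always shown, so a drug-only harm cannot be hidden, and every drug-only pattern examined passes the 10% flag. The row for any treatment-emergent adverse event is unlikely to be empty in a whole arm over 48 weeks, and with events in both arms the constant covariate costs nothing. No link is named, so the column header may simply be generic. A journal article may also leave detail to a fuller plan.

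Most of this stands, and it rules out two stronger readings that a reader might infer. One is that treatment-emergent harms get no usable estimate at all; Step 2 shows otherwise when both arms have events. The other is that a drug-only harm will be reported with p near 1. That needs a Wald p value printed despite the infinite estimate; no Wald test is specified, and the likelihood ratio test on the same data gives 0.003.

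What does not stand is that the conditional wording solves the problem. It permits a blank cell and names no replacement. The flag shows an imbalance but is exceeded by more than half of null variables. Nor is this merely condensed detail: the article prints a model and a table in which two rows cannot carry the stated covariate.

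**Conclusion.** The point holds in a limited form. For two of the ten Table 5 rows the stated covariate does not exist. For any n (%) row with an empty arm, the stated model gives an infinite point estimate and a Wald interval without useful limits. In that case, what the plan guarantees is counts and a flag that about 55% to 58% of null variables exceed, not a between-arm estimate with an interval. The p value could be absent, 0.999 or 0.003 for the same 6 v 0, depending on a choice the plan leaves open; an exact test, which the plan does not mention, gives 0.028.

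This rests on the usual meaning of treatment-emergent (the protocol definition is not shown), 60 or 71 per arm, a logit link and illustrative event counts. The infinite estimate depends on neither the arm size nor the number of events in the other arm. Zero cells are more plausible for sparse rows, such as ECG findings, than for any adverse event.

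**What to change.** In the Safety analyses section and Table 5:

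1. For treatment-emergent adverse events and treatment-emergent qualitative ECG findings, remove the start-of-trial covariate. Report the participant-level risk difference with a Newcombe or Miettinen-Nurminen 95% interval, and Fisher's exact two-sided p where a p value is shown.
2. Name the same method as the fallback for any other n (%) row with a zero cell or a model that does not converge.
3. Keep the baseline-adjusted mixed model for the continuous rows and for binary rows with a start-of-trial value, such as abnormal laboratory analytes.
4. Label the effect measure row by row: mean difference, odds ratio, or risk difference in percentage points.

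The cost is a wording change and a simpler computation. The treatment-emergent rows lose adjustment for centre, which is a minimisation factor. The interval and the exact p can also disagree at the margin: 5 v 0 at 71 per arm gives 7.0 points (0.5 to 15.4) with Fisher p = 0.058. The plan should therefore say that the interval is the main result. Dropping centre and baseline from all n (%) rows would go further than the problem requires.

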## Conclusion

In this article, we followed the Guidelines for the content of statistical analysis plans in clinical trials [2] to provide detailed descriptions of the statistical methods required for carrying out the statistical analysis of the GKT137831 trial. The aim of this prior statistical analysis plan is to minimise reporting bias, supporting both transparency and reproducibility of the trial findings. All statistical analyses will be conducted using R (R Foundation for Statistical Computing, Vienna, Austria; lme4 package for R for fitting linear mixed models) and Stata (StataCorp, College Station, TX, USA). Other software packages such as SPSS or SAS may be used if necessary. The results of the trial are expected to be published, and these results may be used to inform further phase 3 trials for regulatory submission.

## Data Availability

Not applicable.

## Abbreviations

eGFR: Estimated glomerular filtration rate
HbA1c: Glycated haemoglobin
HREC: Human Research Ethics Committee
ITT: Intention to treat
IWRS: Interactive Web Response System
NADPH: Nicotinamide adenine dinucleotide phosphate
PP: Per protocol
SAP: Statistical analysis plan
UACR: Urine albumin–creatinine ratio
